#### **Hematological Dose-Limiting Toxicities:**

- Grade 4 neutropenia regardless of intervention is a DLT.
- Febrile neutropenia (defined as an ANC  $<1000/\text{mm}^3$  with a single temperature of  $>38.3^\circ\text{C}$  [ $101^\circ\text{F}$ ], or a sustained temperature of  $\geq 38^\circ\text{C}$  [ $100.4^\circ\text{F}$ ] for more than 1 hour) is a DLT.
- Grade 3 neutropenia with infection is a DLT (Note: isolated Grade 3 neutropenia without accompanying fever or infection as defined above is not a DLT).
- Grade 4 thrombocytopenia is a DLT.
- Grade 3 thrombocytopenia with bleeding or requiring platelet transfusion is a DLT.
- Grade 4 anemia is a DLT.
- Grade 3 anemia requiring blood transfusion is a DLT.

#### **Non-Hematologic Dose-Limiting Toxicities:**

Any Grade  $\geq 3$  non-hematologic possibly treatment related AE is a DLTs with the following clarifications:

- Grade  $\geq 3$  nausea, vomiting, or diarrhea lasting  $\geq 3$  days despite adequate antiemetic and other supportive care is a DLT.
- Grade  $\geq 3$  fatigue lasting  $\geq 7$  days is a DLT.

- Confirmed DILI meeting Hy's law criteria is a DLT.
- For participants with Grade 2 hepatic transaminase or alkaline phosphatase levels at baseline as a result of liver metastasis or bone metastasis, AST or ALT >10 x ULN or AST or ALT >5 x ULN for  $\geq 14$  days will be considered a DLT
- Clinically important or persistent toxicities (eg, toxicities responsible for significant dose delay) that are not included in the above criteria may also be considered a DLT following review by the investigators and the Sponsor. All DLTs need to represent a clinically significant shift from baseline.
- Grade  $\geq 3$  QTc prolongation is a DLT.
- Grade  $\geq 3$  anaphylaxis is a DLT.

Any toxicity causing greater than 2 weeks of dose delay of either PF-07248144 [REDACTED] is a DLT. In addition, any Grade 5 AE (death) not clearly due to either the underlying disease or other etiologies is a DLT. *Note:* Participants deriving clinical benefit from study intervention who experience a DLT may continue on study at a reduced dose following recovery of the AE to Grade 1 or baseline, only after discussion between the Investigator and Sponsor.

Any dose reduction of either PF-07248144 [REDACTED] due to a treatment-related AE (per protocol) during the first 28 days will be qualified as participant experiencing DLT.

The following AEs will not be adjudicated as DLTs:

- Isolated Grade 3 laboratory abnormalities that are not associated with clinical sequelae and are corrected or resolved to Grade 1 or baseline with supplementation/appropriate management within 72 hours of their onset.

Adverse events consistent with the definition of a DLT observed after the DLT observation period may also be considered in dose escalation decisions and the final determination of the MTD/RDE as monotherapy and in combination.

#### **4.3.6. Maximum Tolerated Dose Definition**

MTD is defined as a dose with true DLT rate from the target toxicity interval. The target interval for the DLT rate is defined as (0.16, 0.33).

#### **4.3.7. Recommended Phase 2 Dose and Recommended Dose for Expansion Definition**

The RP2D is the dose chosen for further investigation based on Phase 1 study results. The monotherapy RDE is the dose chosen for further investigation based on Part 1A dose escalation results. If the MTD proves to be clinically feasible for long term administration in a reasonable number of participants, then this dose becomes the RDE. However, RDE dose might be lower than the MTD. Safety, efficacy, and PK data as well potential exposure-response relationships will be considered in identifying the RDE.

Similarly, based on the safety, tolerability and PK/PD data from Part 1B, [REDACTED], combination dose finding, [REDACTED] RDE will be selected. The final combination “Study” RP2D will be determined after the completion of combination expansion cohorts. Combination RDE may be different from monotherapy RDE due to potential toxicity overlap or drug-drug interaction.

Each dose expansion cohort may investigate more than one dose of each of the study interventions. All dose levels to be evaluated will be informed by available data from dose escalation (including safety, PK/PD, and efficacy) and will not exceed each agent’s MTD. [REDACTED]

After dose expansion, the final “Study” RP2Ds will be determined by the sponsor based on the recommendation from investigators and study team. The determination of “Study” RP2D will be based on safety, tolerability and early signs of clinical efficacy and benefit from both Part 1 dose escalation and Part 2 expansion.

During escalation and prior to an MTD being reached, the sponsor may choose to advance a lower dose into expansion, particularly (but not exclusively) when considering combination cohorts. This decision will be made based on emerging preliminary safety, PK, PD, and/or efficacy data.

#### 4.3.8. [REDACTED]

[REDACTED]

[REDACTED]

[REDACTED]

[REDACTED]

#### 4.4. End of Study Definition

The end of the study is defined as 2 years from the last participant's first dose unless otherwise notified by the sponsor.

### 5. STUDY POPULATION

This study can fulfill its objectives only if appropriate participants are enrolled. The following eligibility criteria are designed to select participants for whom participation in the study is considered appropriate. All relevant medical and nonmedical conditions should be taken into consideration when deciding whether a particular participant is suitable for this protocol.

Prospective approval of protocol deviations to recruitment and enrollment criteria, also known as protocol waivers or exemptions, is not permitted.

During the COVID-19 pandemic, please refer to [Appendix 13 \(Section 10.13\)](#) for additional eligibilities.

#### 5.1. Inclusion Criteria

Participants are eligible to be included in the study only if all of the following criteria apply:

1. Adult participants age  $\geq 18$  years (please follow local regulatory requirements if the legal age of consent for study participation is less than 18 years old). For participants enrolled at clinical sites in Japan: adult participants age  $\geq 20$  years. For participants enrolled at clinical sites in South Korea: adult participants age  $\geq 19$  years.
  - Refer to [Appendix 4](#) for reproductive criteria for male ([Section 10.4.1](#)) and female ([Section 10.4.2](#)) participants.
2. **Part 1 (Dose Escalation) tumor indications and prior lines of therapy**
  - **Part 1A (Monotherapy Dose Escalation):** Histological or cytological diagnosis of locally advanced or metastatic ER+HER2- breast cancer, locally advanced or metastatic CRPC, or locally advanced or metastatic NSCLC that is intolerant or resistant to standard therapy or for which no standard therapy is available.
  - **Part 1B (Combination Dose Escalation):** Histological or cytological diagnosis of locally advanced or metastatic ER+HER2- breast cancer. Participants must have progressed after at least 1 prior line of treatment with an endocrine therapy and CDK4/6 inhibitor in the advanced or metastatic setting.
  - [REDACTED]

[REDACTED]

[REDACTED]

- Intolerance or progression on prior therapies must be documented for study enrollment.

**3. Part 2 (Dose Expansion) tumor indications and prior lines of therapy**

- **Part 2A (ER+HER2- breast cancer 2L+, monotherapy):** Histological or cytological diagnosis of locally advanced or metastatic ER+HER2- breast cancer. Participants must have progressed after at least 1 prior line of CDK4/6 inhibitor and at least 1 prior line of endocrine therapy. Additional Korea specific requirements are provided in [Appendix 8 \(Section 10.8.3\)](#).
- **Part 2B (ER+HER2- breast cancer 2-4L, combination with fulvestrant):**
  - Histological or cytological diagnosis of advanced or metastatic ER+HER2- breast cancer. Participants must have progressive disease after at least 1 prior line of a CDK4/6 inhibitor and at least 1 prior line of endocrine therapy.
  - Participants must not have received more than 3 prior lines of systemic therapies including up to 1 line of cytotoxic chemotherapy for visceral disease in advanced or metastatic setting; Participants may have but are not required to have prior treatment with fulvestrant.

- [REDACTED]

[REDACTED]

[REDACTED]

4. Participants with ER+HER2- advanced or metastatic breast cancer must have documentation of ER-positive tumor ( $\geq 1\%$  positive stained cells) based on most recent tumor biopsy (unless non-measurable disease where most recent documentation will be provided) utilizing an assay consistent with local standards.

5. Participants with ER+HER2- advanced or metastatic breast cancer must have documentation of HER2-negative tumor: HER2-negative tumor is determined as immunohistochemistry score 0/1+ or negative *by in situ* hybridization (FISH/CISH/SISH/DISH) defined as a HER2/CEP17 ratio <2 or for single probe assessment a HER2 copy number <4.
6. Female participants with ER+HER2- advanced or metastatic breast cancer considered to be of childbearing potential (or have tubal ligations only) must be willing to undergo medically induced menopause by treatment with the approved LHRH agonist such as goserelin, leuprolide or equivalent agents to induce chemical menopause.
7. Female participants with ER+HER2- advanced or metastatic breast cancer of nonchildbearing potential must meet at least 1 of the following criteria of achieving postmenopausal status, defined as follows:
  - Cessation of regular menses for at least 12 consecutive months with no alternative pathological or physiological cause; [status may be confirmed with/and have] a serum follicle-stimulating hormone (FSH) level confirming the post menopausal state;
  - Have undergone a documented hysterectomy and/or bilateral oophorectomy;
  - Have medically confirmed ovarian failure. All other female participants (including female participants with tubal ligations) are considered to be of childbearing potential.
8. Participants must have at least 1 measurable lesion as defined by RECIST version 1.1 that has not been previously irradiated.
9. ECOG Performance Status PS 0 or 1 (See [Appendix 12: Section 10.12](#)).
10. Adequate Bone Marrow Function, including:
  - a. ANC  $\geq 1,500/\text{mm}^3$  or  $\geq 1.5 \times 10^9/\text{L}$ ;
  - b. Platelets  $\geq 100,000/\text{mm}^3$  or  $\geq 100 \times 10^9/\text{L}$ ;
  - c. Hemoglobin  $\geq 9 \text{ g/dL}$ .
11. Adequate Renal Function, including:
  - a. Serum creatinine  $\leq 1.5 \times \text{ULN}$  or estimated creatinine clearance GFR  $\geq 60 \text{ mL/min}$  ( $\geq 50 \text{ mL/min}$  for Part 2 dose expansion is acceptable) as calculated using the method standard for the institution. In equivocal cases, a 24 hour urine collection test can be used to estimate the creatinine clearance more accurately.

12. Adequate Liver Function, including:

- a. Total serum bilirubin  $\leq 1.5 \times$  ULN unless the participant has documented Gilbert syndrome;
  - b. AST and ALT  $\leq 2.5 \times$  ULN; AST and ALT  $\leq 3.0 \times$  ULN if there is liver involvement by the tumor for Part 1 dose escalation. AST and ALT  $\leq 5.0 \times$  ULN if there is liver involvement by the tumor for Part 2 dose expansion.
13. Resolved acute effects of any prior therapy to baseline severity or CTCAE Grade  $\leq 1$  except for AEs not constituting a safety risk by investigator judgment.
14. Participants who are willing and able to comply with all scheduled visits, treatment plan, laboratory tests, lifestyle considerations, and other study procedures.
15. Capable of giving signed informed consent as described in [Section 10.1.3](#), which includes compliance with the requirements and restrictions listed in the ICD and in this protocol.

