### 10.4.2. Female Participant Reproductive Inclusion Criteria

- A female participant is eligible to participate if she is not pregnant or breastfeeding (women who are currently breastfeeding and intend to interrupt breastfeeding are excluded from participating), and at least 1 of the following conditions applies:
- Is not a WOCBP (see definitions below in [Section 10.4.3](#)).

OR

- Is a WOCBP and using a contraceptive method that is highly effective (with a failure rate of <1% per year), preferably with low user dependency, as described below during the intervention period and for at least 28 days after the last dose of study intervention, which corresponds to the time needed to eliminate any reproductive safety risk of the study intervention(s). The investigator should evaluate the effectiveness of the contraceptive method in relationship to the first dose of study intervention.
- Is a WOCBP and using a contraceptive method that is highly effective (with a failure rate of <1% per year), with high user dependency, as described below during the intervention period and for at least 28 days after the last dose of study intervention, which corresponds to the time needed to eliminate any reproductive safety risk of the

study intervention(s). In addition, a second effective method of contraception, as described below, must be used. The investigator should evaluate the effectiveness of the contraceptive method in relationship to the first dose of study intervention.

- A WOCBP agrees not to donate eggs (ova, oocytes) for the purpose of reproduction during this period. The investigator should evaluate the effectiveness of the contraceptive method in relationship to the first dose of study intervention.
- The investigator is responsible for review of medical history, menstrual history, and recent sexual activity to decrease the risk for inclusion of a woman with an early undetected pregnancy.

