#### **10.4.3. Woman of Childbearing Potential**

A woman is considered fertile following menarche and until becoming postmenopausal unless permanently sterile (see below).

If fertility is unclear (eg, amenorrhea in adolescents or athletes) and a menstrual cycle cannot be confirmed before the first dose of study intervention, additional evaluation should be considered.

Women in the following categories are not considered WOCBP:

1. Premenopausal female with 1 of the following:
  - Documented hysterectomy;
  - Documented bilateral salpingectomy;
  - Documented bilateral oophorectomy.

For individuals with permanent infertility due to an alternate medical cause other than the above, (eg, mullerian agenesis, androgen insensitivity), investigator discretion should be applied to determining study entry.

Note: Documentation for any of the above categories can come from the site personnel's review of the participant's medical records, medical examination, or medical history interview. The method of documentation should be recorded in the participant's medical record for the study.

2. Postmenopausal female.
  - A postmenopausal state is defined as no menses for 12 months without an alternative medical cause. In addition, a
  - High FSH level in the postmenopausal range must be used to confirm a postmenopausal state in women under 60 years old and not using hormonal

contraception or HRT. When there is a high FSH level, it should be confirmed that there is no other medical cause.

- Female on HRT and whose menopausal status is in doubt will be required to use one of the non-estrogen hormonal highly effective contraception methods if they wish to continue their HRT during the study. Otherwise, they must discontinue HRT to allow confirmation of postmenopausal status before study enrollment.

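### Inclusion criterion 7 accepts hysterectomy alone as postmenopausal status, so a woman with functioning ovaries escapes the ovarian suppression that criterion 6 asks of others

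*Protocol*

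**What the plan says.** All references are to the Protocol.

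Section 5.1, criterion 6, requires ovarian suppression with an LHRH agonist. It covers ER+HER2- women "considered to be of childbearing potential (or have tubal ligations only) must be willing to undergo medically induced menopause".

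Criterion 7 covers ER+HER2- women of nonchildbearing potential, who "must meet at least 1 of the following criteria of achieving postmenopausal status, defined as follows". There are three items: twelve months without menses and with no other cause (with wording on FSH), the surgical item "Have undergone a documented hysterectomy and/or bilateral oophorectomy", and medically confirmed ovarian failure. The closing sentence is "All other female participants (including female participants with tubal ligations) are considered to be of childbearing potential".

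Criterion 1 refers sites to Appendix 4 for the reproductive criteria. Section 10.4.3 there lists who is not a woman of childbearing potential (WOCBP). Group 1 is headed "Premenopausal female with 1 of the following" and contains "Documented hysterectomy", bilateral salpingectomy and bilateral oophorectomy. Group 2 is the postmenopausal woman. She is defined by a year without menses that has no other medical explanation, with a high FSH to confirm it in women under 60 who do not use hormonal contraception or HRT.

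**The concern.** Criterion 7 uses a fertility category as a definition of hormonal status. Hysterectomy makes pregnancy impossible, which is what a contraception section needs to know. It does not show that the ovaries have stopped working, which is what a menopausal criterion in ER+ disease needs to know.

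At stake is the classification and endocrine treatment of an individual participant. In the fulvestrant cohorts she could be treated as postmenopausal while her ovaries still produce estrogen. Section 2.2.6 names postmenopausal women in two of the three fulvestrant indications it lists, including the one for use after endocrine therapy without palbociclib. That section is background and sets no eligibility rule, but it shows why the status matters in Parts 1B and 2B. In the monotherapy parts the visible text shows only unequal handling of women with the same ovarian function. Section 5 does not permit eligibility waivers, so sites will apply the criterion as written.

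**Working it through.** The plan gives no figure to reproduce, so the check sets the rules side by side. Take ER+HER2- women under 60 without confirmed ovarian failure who differ only in past surgery:

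| Past surgery | Ovaries working | Section 10.4.3 | Criterion 7 | LHRH agonist under criterion 6 |
|---|---|---|---|---|
| Tubal ligation only | Yes | WOCBP | No item met; of childbearing potential by the closing sentence | Required |
| Bilateral salpingectomy | Yes | Not a WOCBP | No item met; of childbearing potential by the closing sentence | Required |
| Hysterectomy, ovaries kept | Yes | Not a WOCBP | Surgical item met; postmenopausal, no FSH | Not required |
| Bilateral oophorectomy | No | Not a WOCBP | Surgical item met; postmenopausal | Not required, not needed |

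The first three women have the same ovarian function. Only the third escapes suppression.

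1. *Does hysterectomy alone meet criterion 7?* Yes. One item is enough, and the surgical item joins its two operations with an and/or.
2. *Does criterion 6 reach her?* No. She is not of childbearing potential and does not have tubal ligation only. The closing sentence of criterion 7 catches only women who meet no item, and she has met one.
3. *Is criterion 6 only about contraception?* That is hard to maintain. It asks for medically induced menopause, and it asks this of women with tubal ligation, although Section 10.4.4 lists bilateral tubal occlusion among the highly effective, low-user-dependency methods. Ovarian function explains the rule; contraception alone does not.
4. *Would she be postmenopausal by the protocol's other definition?* Not from the operation. After hysterectomy the absence of menses has an obvious medical explanation, so it cannot establish menopause under Section 10.4.3. The first item of criterion 7 likewise rules out absent menses that have another cause. Under 60, Section 10.4.3 would also ask for FSH; the surgical item asks for none.
5. *Does any other visible criterion require suppression?* None was found.

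Scale, from the document's own counts:

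- Part 2B plans about 30 participants (Section 9.2.2), so one woman is 1/30 = 3.3%.
- By 12 September 2022 Part 2B had treated 8 (Section 2.2.4), leaving about 30 − 8 = 22 of that cohort, plus any enrolled at an alternative dose.
- Part 1B had treated 4 and its expansion dose had been identified; Part 2A had treated 33 against about 30 planned. A wording change would reach few or none in those parts.

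**The case against.** Four objections deserve an answer.

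*Heading in Section 10.4.3.* A reader might infer a flat contradiction: hysterectomy stands under a premenopausal heading in Appendix 4 and under postmenopausal status in criterion 7. The documents do not support that much. The same heading also covers bilateral oophorectomy, which does end ovarian function, so it seems to mark surgical sterility before natural menopause and not current hormonal state. Nor do the two sections give sites opposing instructions: both leave her outside childbearing potential. This objection stands. The point rests on the separate postmenopausal definition in 10.4.3 and on the evident purpose of criterion 6.

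*Redaction.* The fulvestrant administration text, much of Sections 6.5.2 and 6.5.3, and several exclusion criteria are blacked out, and sites are also sent to the fulvestrant label. A suppression rule could sit there. This stands as a condition on the treatment gap. It would not make the visible definition in criterion 7 correct.

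*Physician discretion.* A reader might infer that Section 6.5.3, which opens by barring further anti-tumor treatment, stops a physician from suppressing this woman. That does not follow. Criterion 6 itself requires an LHRH agonist during the study, Section 6.5 permits necessary concomitant treatment, and the rest of 6.5.3 is redacted. Suppression is not visibly forbidden; it is only not required.

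*Size.* One woman in a Part 1B of 6 to 9 would be 1/9 = 11% to 1/6 = 17%, but that holds for any single participant and shows no effect. This also stands.

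**Conclusion.** The point holds as a wrong classification rule of low frequency. Criterion 7 counts an ER+HER2- woman with a hysterectomy and functioning ovaries as postmenopausal without FSH, and she thereby leaves the reach of criterion 6, while women with tubal ligation and the same ovarian function stay inside it.

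The practical reach is mainly the rest of Part 2B, at 3.3% of the planned cohort per affected woman. The protocol gives no figure for how many such women would enroll; the number is probably small. The treatment consequence assumes that no redacted passage or label instruction already requires suppression. The misdefinition in criterion 7 needs no such assumption.

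A reader might go further and suspect bias in the Part 2 response comparisons or in the safety endpoints. Nothing in the documents supports that, and it is not claimed.

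**What to change.** Make three linked changes in Section 5.1.

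- **Criterion 7, surgical item.** Replace with: *documented bilateral oophorectomy (with or without hysterectomy), or documented hysterectomy with age 60 or older or, under 60 and not on hormonal contraception or HRT, an FSH in the postmenopausal range.* The age limit and the exception follow Section 10.4.3.
- **Criterion 6, scope.** Extend to: *of childbearing potential, or with tubal ligations only, or with hysterectomy and at least one retained ovary and not confirmed postmenopausal under criterion 7.*
- **Criterion 7, closing sentence.** Add: *except women with documented hysterectomy, who are not WOCBP under 10.4.3 and need no contraception or pregnancy testing, but must meet criterion 6 if not confirmed postmenopausal.*

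The third change is needed. Without it, a woman under 60 with a hysterectomy and a premenopausal FSH would meet no item of criterion 7. The closing sentence would then class her as of childbearing potential, against Section 10.4.3, and bring in pregnancy testing that she cannot need.

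The cost is a few words in an amendment and a local screening FSH for the few women under 60 with a hysterectomy and a retained ovary. FSH is not among the laboratory tests in Table 13, but the protocol already relies on it to confirm menopause.
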